### 8.6.4. LightPath® assessment

The WLE specimen will be examined by CLI + FAR LightPath® imaging at the time of the surgical procedure. All LightPath® images will be performed within approximately 145 minutes post-injection of  $^{18}\text{F}$ -FDG. If imaging is delayed for any reason, the reason must be recorded on the CRF. Imaging must be performed without unnecessary delay and following the acquisition times set out in the IFU, in order to avoid any degradation in specimen quality prior to transfer to the tissue bank / pathology department for routine analyses.

The operating surgeon will interpret the recorded CLI + FAR LightPath® Images. It will be at the surgeon's discretion to choose how to act on the CLI + FAR LightPath® images.

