## 2.4. Schedule of Events

| Procedures                                                                          | Screening | Day of Surgery | Discharge | Study Completion at MDT decision on re-operation (1-2 weeks) |
|-------------------------------------------------------------------------------------|-----------|----------------|-----------|--------------------------------------------------------------|
| Visit                                                                        | 1  | 2       | 2  | 3                                                     |
| Informed Consent                                                                    | X         |                |           |                                                              |
| Inclusion/Exclusion                                                                 | X         |                |           |                                                              |
| Demographics, Medical History                                                       | X         |                |           |                                                              |
| Biomarkers (ER/PR/HER2/other, according to local practice)                          | X         |                |           |                                                              |
| Injection of 99m Tc                                                      |           | X              |           |                                                              |
| Injection of  F-FDG                                                    |           | X              |           |                                                              |
| Standard-of-care surgical procedure                                                 |           | X              |           |                                                              |
| Intra-operative specimen x-ray analysis of WLE specimen as per standard-of-care     |           | X              |           |                                                              |
| LightPath® imaging of WLE specimen                                                  |           | X              |           |                                                              |

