| Cavity shaving if indicated by LightPath® Imaging and/or specimen x-ray             |           | X              |           |                                                              |
| LightPath® imaging of cavity shaving, if applicable                                 |           | X              |           |                                                              |
| Histopathology analysis of WLE specimen and cavity shavings as per standard-of-care |           | X              |           |                                                              |
| Study related Adverse Events                                                        |           | X              | X         | X                                                            |
| Multidisciplinary team decision on re-operation ( within 1-2 weeks )         |           |                |           | X                                                            |

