Tumours fail to be completely excised because the surgeon only has the visual appearance of the tumour, palpation and specimen x-ray to differentiate malignant from benign tissue. A standardised approach to margin assessment can reduce residual disease and likelihood of re-excision (Bolger et al 2015, Merrill et al 2016). Currently available technologies for image-guided cancer surgery either have low sensitivity (for example, ultrasound, optical coherence tomography) or require lengthy regulatory development of novel contrast agents (e.g., targeted fluorescence or photoacoustic imaging). A number of techniques have been investigated including frozen section analysis and touch imprint cytology. However, no single technique has been accepted as standard of care due to issues of practicality, increased surgery time, limited clinical utility, limited sensitivity and specificity and cost (National Institute for Health and Care Excellence (NICE). (2009)). Consequently, less than 5% of hospitals that perform WLE currently utilise intra-operative cytology or frozen section pathology analysis of tumour margins (Bydlon et al 2012).

Optical imaging has been considered for intra-operative imaging since the original use of fluorescein in 1947 (Moore 1947). It offers an attractive solution to the problem of intra-operative tumour margin assessment, as it is fast and non-destructive. A variety of different methods of optical imaging have been proposed, including intra-operative radiography, radiofrequency spectroscopy, Raman spectroscopy, fluorescence spectroscopy and optical coherence tomography. Each has limitations, either in sensitivity and specificity, shallow penetration, poor definition or time and cost to develop targeted fluorescent agents.

In conclusion, a key problem that currently affects the success of WLE is the lack of accurate, real-time techniques to assess tumour margins intra-operatively. Therefore, there is a clear unmet need for new intra-operative techniques that can accurately and adequately assess tumour margins, thereby reducing the number of patients that need to undergo a re-operation.

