### 6.2. Secondary outcome measures

- Agreement between margin status of cavity shavings as determined by intraoperative CLI + FAR LightPath® imaging and post-operative histopathology.
- Agreement between margin status of WLE specimens as determined by intraoperative CLI + FAR LightPath® imaging and routine intraoperative specimen x-ray.
- Re-operation rate within the study cohort compared to general breast cancer population undergoing a WLE at Guy's Hospital.
- Time added to operating procedure.

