### 8.6.2. BCS only

Participants scheduled to have BCS will be administered  $^{18}\text{F}$ -FDG intravenously in the Nuclear Medicine Department, approximately 145 minutes prior to CLI + FAR LightPath® imaging. BCS will be performed as per standard of care. Following resection, the WLE specimen and shavings (if any) will be examined intraoperatively using CLI + FAR LightPath® imaging. If the surgeons detect a positive signal, they will perform cavity shavings of the resection cavity area corresponding to the positive signal area. It will be at the surgeon's discretion to choose whether to act based upon the intraoperative LightPath® images.

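### Nothing fixes the reading order or locks the LightPath call, so specimen x-ray information can carry over into it; this mainly threatens the LightPath versus x-ray agreement outcome

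*Protocol*

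**What the plan says.** Section 8.6.4 states that "The operating surgeon will interpret the recorded CLI + FAR" images, and leaves it to that surgeon how to act on them. No other reader is named. Section 8.6.2 gives the only operational rule for a positive result: "If the surgeons detect a positive signal, they will perform cavity shavings". It sets no threshold or score.

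The schedule in section 2.4 includes "Intra-operative specimen x-ray analysis of WLE specimen as per standard-of-care" on the day of surgery, in the row directly above LightPath imaging of the WLE specimen. A later row reads "Cavity shaving if indicated by LightPath® Imaging and/or specimen x-ray", so both results can feed the same decision. The background in section 3.1 says that "the surgeon only has the visual appearance of the tumour, palpation and specimen x-ray" to tell malignant from benign tissue.

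Section 6.2 lists, as a secondary outcome, agreement on WLE margin status between "CLI + FAR LightPath® imaging and routine intraoperative specimen x-ray". Section 11.7.2 analyses it in the same way as the primary outcome. Under sections 6 and 11.7.1, the primary aim is the accuracy of CLI + FAR against histopathology, reported as sensitivity, specificity and overall accuracy.

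**The concern.** Agreement between two tests is informative only if neither read is guided by the other. Here one person may hold the x-ray result while making a subjective LightPath call on the same specimen. If equivocal signals are settled with the x-ray in mind, the agreement outcome partly measures the reader's consistency with himself or herself.

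The primary outcome is exposed less directly. A LightPath call made with the x-ray in hand describes LightPath plus x-ray, whereas section 6 sets out to measure CLI + FAR. Analysis cannot repair this later, because an independent call that was never recorded cannot be recovered. Reading order and recording are theatre procedures, so they belong in the protocol.

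**Working it through.** **Text check.** The places where a safeguard could stand are these:
- Section 8.6.4 names the reader and requires a recorded reason if imaging is delayed. It sets no reading order and no recorded margin call.
- Sections 8.6.2 and 8.6.5 describe imaging and the response to a positive signal. They do not mention the x-ray.
- Section 8.6.3 sends information on the surgical procedure to the case report form (CRF). It does not mention a LightPath call or its time.
- Section 2.4 lists both procedures on the same day. Row order in a schedule is not a reading order.
- Sections 11.7.1 and 11.7.2 analyse the calls and make no provision for a shared reader.

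None of them masks the LightPath read to the x-ray, orders the reads or locks the call.

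**Illustration.** The protocol states no figure for this point, so there is none to reproduce. Inputs from section 11.6.2: prevalence of positive margins 20%, LightPath sensitivity (SeL) 95%, specificity (SpL) 90%, N = 54. Assumed, because the protocol gives no x-ray accuracy: x-ray sensitivity (SeX) 60%, specificity (SpX) 90%, and independence of the two tests given histology.

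Agreement of independent reads:
A = 0.2 × (0.95 × 0.60 + 0.05 × 0.40) + 0.8 × (0.90 × 0.90 + 0.10 × 0.10) = 0.118 + 0.656 = 0.774. Discordance is 1 − 0.774 = 0.226.

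*Override:* a share c of discordant calls is recorded as the x-ray result.
- Agreement = A + c(1 − A). For c = 10%: 0.774 + 0.0226 = 0.797. For c = 25%: 0.774 + 0.0565 = 0.831.
- Sensitivity = SeL + c(SeX − SeL). For c = 10%: 0.95 − 0.035 = 0.915. For c = 25%: 0.95 − 0.0875 = 0.8625.
- Specificity = SpL + c(SpX − SpL) = 0.90. It stays put only because both specificities were set at 90%.

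*Upgrading only:* a share c of LightPath-negative, x-ray-positive reads is recorded as positive.
- Probability of such a read = 0.2 × 0.05 × 0.60 + 0.8 × 0.90 × 0.10 = 0.078.
- For c = 25%, agreement = 0.774 + 0.25 × 0.078 = 0.794; sensitivity = 0.95 + 0.25 × 0.05 × 0.60 = 0.9575; specificity = 0.90 − 0.25 × 0.90 × 0.10 = 0.8775.

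The same formulas with other assumed x-ray values:

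| X-ray Se/Sp (assumed) | Mechanism | Agreement | Sensitivity | Specificity |
|---|---|---|---|---|
| 50%/85% | none | 72.4% | 95% | 90% |
| 50%/85% | override 25% | 79.3% | 83.8% | 88.8% |
| 50%/85% | upgrade 50% | 78.1% | 96.3% | 83.3% |
| 70%/80% | none | 72.8% | 95% | 90% |
| 70%/80% | override 25% | 79.6% | 88.8% | 87.5% |
| 70%/80% | upgrade 50% | 80.4% | 96.8% | 81.0% |

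Agreement rises in every row with carry-over. Sensitivity moves down under override and up under upgrading.

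**Scale in patients.** Among 54 specimens, the 25% override adds 54 × 0.0565 ≈ 3 agreeing pairs. With 0.2 × 54 = 10.8 positive specimens expected, it costs 10.8 × 0.0875 ≈ 0.9 of a true positive. The exact 95% interval for 10 of 11 runs from 58.7% to 99.8%, so the shift in sensitivity would be well inside sampling error.

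**The case against.** The strongest reply is that the surgeon is the intended user. The images exist to inform that person during the operation, and accuracy in the user's hands with the usual clinical information is a legitimate target. Histopathology comes afterwards, so the call cannot be coloured by the reference standard. Both points stand, and they make the primary-outcome part of this concern the weaker one. They do not rescue an outcome defined as agreement between two tests.

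A reader might infer that x-ray information does carry over, so that neither estimate is usable. The documents do not support that. They do not say who reads the x-ray or when, section 3.1 is general background, and the shaving row in section 2.4 concerns a surgical decision, not how an image is classified. Agreement can still be estimated, with a possible upward bias.

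A reader might also infer that LightPath sensitivity would be understated. The upgrading scenarios show the opposite, so the direction is open.

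The CRF and the device's instructions for use are not at hand and may say more about recording. Finally, holding back a standard-of-care x-ray in every case is not shown to be free of cost. BCS is to follow standard of care, and time added to the operation is itself an outcome.

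**Conclusion.** The point holds as an unguarded risk. As written, the plan lets one reader hold the x-ray result before making a threshold-free LightPath call, and then analyses agreement between the two.

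The main effect is on the x-ray agreement outcome. In the base illustration it rises from 77% to 80-83% when 10% to 25% of discordant calls follow the x-ray. Recorded sensitivity then falls to 91.5-86%, but it rises, with lower specificity, if only x-ray positives are upgraded. The upward direction for agreement needs only that the x-ray pulls the LightPath call towards itself. The sizes rest on assumed x-ray accuracy, conditional independence and assumed shares of altered calls. The change is worth making because it is cheap and the loss cannot be repaired in analysis.

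**What to change.** In section 8.6.4, require the surgeon to enter a positive or negative LightPath call for each margin on the CRF, with the time, before deciding on a shaving. Where this does not hold up standard-of-care use of the x-ray, the entry should also precede viewing the x-ray. Add a CRF item for whether the x-ray had already been seen.

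In sections 11.7.1 and 11.7.2, use the locked call for the primary and x-ray-agreement analyses. Base the main x-ray-agreement estimate on calls made before the x-ray was seen, give their number, and report the rest as unmasked. Both results stay available for the surgical decision.

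The cost is a few CRF fields and possibly a short wait before the x-ray is viewed. Three limits remain:
- What the surgeon knows from palpation and appearance is not removed.
- The main agreement estimate may rest on fewer than 54 specimens.
- If the same surgeon then reads the x-ray, that read is not masked to LightPath, and the report should say so.

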### 8.6.5. Imaging of the WLE specimen

The WLE specimen will be placed in the LightPath® specimen holder to maintain orientation during examination. Once the WLE specimen has been fixed in the

specimen holder it will be positioned inside the light-tight imaging chamber of the LightPath® System and imaged using the white-light video camera to assess correct positioning of the sample in imaging system. Once positioned correctly, CLI LightPath® Imaging will be performed using the LightPath®'s emCCD camera. Subsequently, the specimen will be covered with a scintillating film for FAR imaging with the LightPath®'s emCCD camera.

#### **8.6.6. Imaging of the cavity shavings**

CLI + FAR LightPath® imaging of cavity shavings (if any) is performed similar to imaging of the WLE specimen, as described above.

#### **8.6.7. Radiation safety**

Prior to starting the study, all staff will have received training sessions in accordance with the hospital Nuclear Medicine and Radiation Safety policies and procedures. This is to ensure all staff are familiar with the radiation control procedures, occupational risks, and to learn how to minimise exposure without compromising patient care.

#### **8.6.8. Histopathological assessment**

The WLE specimens and cavity shavings will then be examined according to the standard of care histopathology analysis as per the routine pathway at Synlab, Histopathology laboratories, St. Thomas' Hospital. Details of tumour dimensions along with all other histopathology minimum dataset items will be recorded. The distance from the tumour to the radial margins (medial, lateral, superior, inferior, posterior and anterior) will be recorded.

For the histopathology central assessment of the WLE, margins are defined (Toss et al 2017) as either:

- Invasive carcinoma – positive <1mm; negative ≥1mm
- DCIS - positive: <2mm; negative ≥2mm

#### **8.6.9. Safety**

Details of any adverse events will be recorded.

### **8.7. Follow-up**

Adverse events will be recorded until discharge, or for 24 hours after the first study procedure, whichever is sooner.

Participants will return for a study completion visit. Participants will return following the MDT recommendation whether to re-operate (1-2 weeks after completion of the initially planned surgery).

## **8.8. Study Duration**

### **8.8.1. Duration of Subject Participation**

The point of enrolment in the study is the point at which the subject provides written informed consent and participation in the treatment phase ends at the conclusion of surgery. Adverse events will be recorded until discharge, or for 24 hours after the first study procedure, whichever is sooner. Participants will return for a study completion visit at the time of the MDT decision whether to re-operate (1-2 weeks after completion of the initially planned surgery).

### **8.8.2. Duration of the Clinical Study**

It is anticipated that recruitment of up to 60 subjects will take approximately 24 months.

## **8.9. Withdrawal of Subjects**

A subject may withdraw from the study at any time. If a subject chooses to withdraw their consent, no additional study related procedures will be performed. Subjects will continue to receive standard of care treatment and follow-up. The Investigator should endeavour to find out the reasons, if any, for withdrawal from the subject and document this in the CRF.

## **8.10. Handling of Radioactive Materials**

All staff will follow local systems of work to ensure that all exposures are "as low as reasonably practicable" (ALARP), in accordance with the Approved Code of Practice and Guidance L121 - Ionising Radiations Regulations 2017. It is unlikely that the removed tissue samples will be a source of radiation risk to the staff handling them, but care may need to be taken when disposing of clinical waste generated from samples. A risk assessment will be performed prior to the study starting and appropriate procedures put in place. Thorough contamination monitoring will be completed in areas in which radionuclides have been present.

## **9. Study Monitoring and Auditing**

The Chief Investigator will be responsible for the ongoing management of the study. The Sponsor will monitor and conduct audits on a selection of studies in its clinical research portfolio. Monitoring and auditing will be conducted in accordance with the UK Policy Framework for Health and Social Care 2017 and in accordance with the Sponsor's monitoring and audit procedures.

## **10. Adverse Events Definition and Reporting**

### **10.1. Adverse Event Definition**

An adverse event (AE) is any untoward medical occurrence in a participant or participant administered a pharmaceutical product (or surgery in this study) and which does not necessarily have a causal relationship with this treatment. An AE can therefore be any unfavourable and unintended sign (including an abnormal laboratory finding), symptom, or disease temporally associated with the use of a

medicinal product as part of a clinical study, whether or not related to the medicinal product (or surgery).

All AEs, either observed by the Investigator or reported by the participant, must be reported immediately, and no later than 24 hours of becoming aware of the event, to the Sponsor. To report an AE, the Principal Investigator (PI) will complete an AE report form or other relevant form located in the Case Report Form. The report will include the following information: nature, severity, date of onset, duration, course and history of the adverse event/adverse device effect and causality.

Recording of AEs will begin with the commencement of the first study procedure. As all study procedures are completed prior to the end of surgery and the radiopharmaceuticals have short physical half-lives, AE recording will conclude when the subject is discharged from hospital, or 24 hours following the first study procedure (whichever is sooner). Any adverse event identified in this period considered by the Principal Investigator (PI) to be related to a study procedure will be followed until resolution or for 30 days, whichever is sooner.

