#### **8.6. Day of surgery**

##### **8.6.1. Radiopharmaceutical administration**

Prior to her surgery, the participant will be prepared for surgery in accordance with the local hospital standard of care. The following information/procedures will be completed on the day of surgery or the day before surgery by a designated team trained in administering radiopharmaceuticals:

- Administration of  $^{99m}\text{Tc}$  tracer prior to the administration  $^{18}\text{F}$ -FDG
- Administration of  $^{18}\text{F}$ -FDG.

Administration of  $^{18}\text{F}$ -FDG will be scheduled accordingly, to ensure the LightPath® images will be taken approximately 145 minutes post-injection of  $^{18}\text{F}$ -FDG.

Work-up and preparation for surgery will be performed as per standard of care.

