## 10.3. Anticipated Adverse Events

Within the context of BS EN 13612 (2002) and with the knowledge that the excision of tissue will not be outside of the normal practice as deemed appropriate by the PI, the LightPath® Imaging System cannot be associated with adverse events.

The radiopharmaceuticals used in this study are commonly administered at doses required by this protocol with no reported safety issues. Therefore, no AEs related to the administration of radiopharmaceuticals are anticipated.

The following are known complications of breast surgery, sentinel lymph node biopsy (SLNB) and axillary lymph node dissection (ALND) (Vitug and Newman 2007), and are anticipated procedure-related AEs:

- Wound infection (including cellulitis and abscess formation)
- Seroma
- Haematoma
- Pain
- Lymphoedema
- Neurosensory disturbance in the upper limb
- Allergic reaction to blue dye

The participants may have additional cavity shavings compared to standard of care surgery at the Investigator's discretion. Risks added by this minor addition to the already major procedures of standard of care surgery are expected to be minimal.

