### 10.6. Adverse Event Reporting

AEs occurring from the first study procedure until the end of follow-up will be reported by completing the relevant section of the CRF. AEs judged by the CI to be related to the standard care of the participant and unrelated to any study procedure do not require to be reported.

The following information will be recorded in the adverse event section of the CRF:

- The signs, symptoms, or diagnosis of the event
- The date and time of onset and resolution of the event
- The adverse event severity using the criteria outlined above
- The relationship of the event to the study procedures as outlined above
- The seriousness of the event as outlined above;
- A list of any required therapy, medication, treatment, or diagnostic procedure
- Any additional data which might be relevant to the event.

The CI is responsible for the appropriate medical management of all adverse events and for the personal safety and wellbeing of the participants.

In addition, a positive sterility test result post-release for a batch which has been administered to patients will be classified as an Adverse Event of Special Interest (AESI). For this reason, infections that could be signs and symptoms possibly related

to bacterial endotoxin will be considered AESI and be immediately reported to the Sponsor even if non-serious. All AESI must be reported in the same manner as SAE reporting and will be handled in the same way.

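### The protocol gives incompatible adverse event recording periods: discharge or 24 hours in three sections, the end of follow-up or the 1-2 week completion visit in two other places

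*Protocol*

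**What the plan says.** Three sections of the protocol set a short window. Section 10.1: "AE recording will conclude when the subject is discharged from hospital, or 24 hours following the first study procedure (whichever is sooner"). Section 8.7 says the same: "Adverse events will be recorded until discharge, or for 24 hours after the first study procedure, whichever is sooner". Section 8.8.1 repeats that sentence. Section 10.1 gives a reason: the study procedures are over by the end of surgery, and the tracers decay quickly.

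Two other places run longer. Section 10.6: "AEs occurring from the first study procedure until the end of follow-up will be reported by completing the relevant section of the CRF". The Schedule of Events (section 2.4) has a row "Study related Adverse Events" marked at the day of surgery, at discharge, and in the column "Study Completion at MDT decision on re-operation (1-2 weeks").

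On what might be recorded, section 10.3 lists seven anticipated procedure-related events, beginning with "Wound infection (including cellulitis and abscess formation") and including seroma, haematoma and lymphoedema. Sections 7.2.1 and 7.2.2 name extra cavity shavings prompted by the images as a risk to participants. Section 10.6 exempts from reporting those events that are judged due to standard care and unrelated to any study procedure. Section 11.7.3 summarises study-related events on the ITT set.

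**The concern.** A site that follows section 10.1 closes the adverse event record within a day. A site that follows section 10.6 and the Schedule of Events keeps it open until the completion visit. The two practices give different safety data from the same patients, and section 11.7.3 does not say which period its summary covers.

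The imaging result can lead the surgeon to remove more tissue. Any harm from that is surgical, and a window justified by tracer decay is not designed to catch it. If the short rule is followed, a low event count could reflect when recording stopped rather than how well patients did.

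**Working it through.** The protocol gives no numerical justification for the window, so there is no figure to reproduce. The check compares the passages and adds simple window arithmetic.

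**1. The periods side by side**
- Sections 8.7, 8.8.1 and 10.1: first study procedure to the sooner of discharge or 24 hours.
- Section 10.6: first study procedure to the end of follow-up, for events *occurring* in that time.
- Schedule of Events: collected at day of surgery, discharge and visit 3 (1-2 weeks).

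Section 10.6 does not define the end of follow-up. The completion visit is the only post-discharge contact planned. It is described in section 8.7, which is headed Follow-up, and the synopsis times the primary analysis from completion of the follow-up visit. The natural reading is therefore visit 3.

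**2. Share of the longer period that the short window covers**
- Inputs: 24 h (section 10.1); 1-2 weeks after surgery = 7 × 24 = 168 h to 14 × 24 = 336 h (sections 2.4 and 8.7).
- 24 / 168 = 14.3%; 24 / 336 = 7.1%.
- Left uncovered: 7 − 1 = 6 days to 14 − 1 = 13 days.
- These shares are upper bounds. Discharge before 24 hours shortens the window, and the 1-2 weeks are counted from surgery, whereas the 24 hours start earlier, at the first study procedure.

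**3. Time left after imaging**
- Inputs: imaging about 145 minutes after the FDG injection (section 8.6.1). Assumption: FDG is the first study procedure.
- 24 − 145/60 = 24 − 2.42 = 21.6 h at most, and less with earlier discharge.

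**4. Does the stated reason fit?**
- Half-lives: 110 minutes for the FDG label (section 4.1.2) and 6.02 h for the technetium tracer (section 4.2.2).
- FDG: 1440 / 110 = 13.1 half-lives in 24 h; 0.5^13.1 leaves about 0.01%.
- Technetium: 24 / 6.02 = 4.0 half-lives in 24 h; 0.5^3.99 leaves about 6.3%.
- So a 24-hour window is reasonable for tracer effects. Yet section 10.3 anticipates no radiopharmaceutical events; the list it does give is surgical. The shaving ends with the operation, but its consequences need not.

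**5. Do other provisions close the gap?**
- The follow-up to resolution or 30 days in section 10.1 applies only to events identified inside the short window.
- Section 10.7 follows serious events up to 30 days after participation ends, but does not clearly extend the period in which a new event must be recorded.

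**6. A test case**
Suppose a wound infection appears on day 5 at the site of an image-directed shaving and is judged possibly related. Section 10.6 requires it to be reported. Section 10.1 has already closed the record. Both cannot be followed.

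**The case against.** The best defence is that the short window is reasoned and stated three times, against two places that run longer. The mark at visit 3 in the Schedule of Events could mean only that events already identified are followed up there. Most of the listed complications belong to standard surgery, and section 10.6 exempts events unrelated to study procedures. Section 10.3 expects the risk added by shavings to be minimal, and safety is neither a primary nor a secondary outcome (sections 6.1 and 6.2).

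Part of this stands. The documents do not dictate which period the sponsor must adopt, and the exemption reduces the number of events at issue. But the follow-up reading cannot rescue section 10.6, which speaks of events occurring until the end of follow-up. The exemption does not remove the problem either: whether an event is due to standard care or to an image-directed shaving can be judged only if it is recorded.

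A reader might infer more than the documents support:
- *That most anticipated complications would be missed.* The protocol gives no onset times. Assuming that infection, seroma and lymphoedema come later gives three of seven, which is not most; lymphoedema may also appear after the completion visit.
- *That infections in general are events of special interest.* Section 10.6 refers to "infections that could be signs and symptoms possibly related" to bacterial endotoxin, in the context of a failed batch sterility test. Wound infections as such are not covered.
- *That extra tissue removal is the only physical effect of the intervention.* Section 7.2.2 also names FDG exposure and its administration, and section 7.2.4 the masking of sentinel nodes.
- *That the clock could run out on the operating day.* Section 8.6.1 says the radiopharmaceutical steps "will be completed on the day of surgery or the day before surgery", but FDG must be given about 145 minutes before imaging, and the Schedule of Events puts both injections on the day of surgery. Only the technetium tracer could come a day earlier, and it is given as standard care, so it is arguably not a study procedure.
- *That the study would report zero events in 60 patients.* Pain, dye allergy and early haematoma can fall inside the window. A confidence limit for zero events would not measure what was missed.

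**Conclusion.** The point holds as an inconsistency with a practical consequence. Sections 8.7, 8.8.1 and 10.1 cannot be reconciled with section 10.6, and they conflict with the plain reading of the Schedule of Events. Under the short rule, recording covers at most 7-14% of the time to the completion visit and leaves 6-13 days out.

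The loss in recorded events cannot be quantified from the protocol. It rests on the assumption that some listed complications, such as wound infection and seroma, usually appear after the first day. On that assumption, several anticipated complications could be missed, including some attributable to image-directed shavings. The primary accuracy analysis is unaffected. The contradiction should be corrected because the safety summary depends on it.

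**What to change.** Reconcile the Schedule of Events and sections 8.7, 8.8.1, 10.1 and 10.6 to one adverse event recording period, and say in section 10.6 what the end of follow-up means. The simplest course is to align 8.7, 8.8.1 and 10.1 with the Schedule of Events and 10.6: record from the first study procedure through the study completion visit for every participant. If the sponsor prefers the short window, 10.6 and the Schedule of Events must change instead, and the safety summary should state that it covers at most the first 24 hours.

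The aligned version uses a visit that already takes place. It costs a protocol amendment, one adverse event question at that visit and slightly more data to code. Treatment does not change, and section 11.7.3 needs no new analysis.
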